#### Efficacy Evaluation of the Integrated Intervention

##### Design

We will conduct a pre-test/post-test experimental design with a 1-month follow-up.

Two independent groups to which patients will be randomly assigned will be considered. One group will undergo a traditional CBT treatment of 16 sessions (the CBT group), while the second group will undergo the integrated treatment, consisting of 8 CBT sessions and 8 sessions of psychotherapy based on VR cue-exposure therapy, each with a different environment (the CBT + VR group). Each session will last 1 h. To better control the effects of the training in VR on pathological gamblers, the psychophysiological parameters of craving will be measured through biofeedback and VAS at each session of the training (multi-method measurement of craving).

To verify the efficacy of the intervention, one measurement session is planned before the beginning of the treatment (pre-test), and one at the end of the treatment (post-test). For the assessment of the maintenance of any changes at post-test, an additional measurement is planned 1 month after the end of the treatment (follow-up). The three measurement sessions are planned for both the CBT group and the CBT + VR group. In each measurement session, perceived self-efficacy in managing gambling behavior, craving, gambling-related cognitive distortions, impulsivity, personality traits, and pathological gambling symptoms will be measured in both groups.

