## Data Analysis

In general, all the patients' demographic and clinical characteristics will be summarized using descriptive statistical methods. In particular, mean, median, and standard deviations will be used for symmetrically distributed continuous variables, median and interquartile distance for asymmetrically distributed continuous variables, and frequency distributions for categorical variables. Multi-method analysis of craving measurement in order to draw up a physiological and psychometric profile of craving (using biofeedback) will be performed. This analysis will be conducted through linear correlation measures. For the analysis of the efficacy of the training course for the treatment providers, Student's *t*-tests for dependent samples or Wilcoxon's non-parametric test for paired samples will be used. Contingency tables and McNemar tests may also be used. For the analysis of the efficacy of the CBT + VR group compared to the CBT group, a mixed ANOVA will be performed for repeated measures with *Time* as within factor (pre-test/post-test/follow-up) and *Group* as between factor (the CBT + VR group/the CBT group).

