Moreover, we will pay attention to the issue of an attrition rate. We are expecting to find a retention rate of at least 80% (78, 79) to avoid that participant loss will bias research outcomes. After that, we will check for any significant difference between the two treatment groups (CBT and CBT + VR) to verify if there is a differential attrition rate. In particular, we will compare the average number of meetings attended by the participants between the two treatment groups through *t*-tests, and we will compare the presence of drop-outs across the two groups through Chi-square tests. Moreover, we will determine if there are any significant differences (at the baseline) between participants who will complete the post-test session and those who will not in order to verify if specific subgroups of participants have a higher drop-out risk. This analysis will be conducted separately for each group. If any significant differences between participants of the two treatment groups will be found, we will verify that systematic attrition does not occur and we will conduct the analyses to verify the effects of the two interventions (CBT and CBT + VR) with the participants who completed the baseline and post-test assessments. Those lost to post tests will be excluded. If significant differences between participants of the two treatment groups will be found for the average number of meetings attended and the treatment drop-out, and participants who will complete the post-test session will be significantly different from those who will not, subsequent analyses will be conducted by using the last observation carried forward (LOCF) to assess the effects of attrition. Furthermore, we will examine within-group changes in outcomes as a function of session attendance to assess the effects of intervention non-compliance on outcomes. These subsequent analyses will be conducted, not excluding participants who will be lost to post-test and by imputing values for the follow-up variables for the participants who will not complete the post-test assessment.

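### The analysis-set, exclusion and imputation rules are defined on post-test completion only and do not fit the three-occasion mixed ANOVA

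*Protocol article*

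**What the plan says.** The Data Analysis section of the protocol article compares the two arms with a mixed ANOVA that has Group as the between factor and Time as the "within factor (pre-test/post-test/follow-up"). The follow-up is a separate visit. According to the Design section, "an additional measurement is planned 1 month after the end of the treatment (follow-up").

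The attrition paragraph of the Data Analysis section then sets four rules:

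- **Completer comparison:** baseline differences are examined between "participants who will complete the post-test session and those who will not".
- **Analysis set:** the effects of the interventions are analysed "with the participants who completed the baseline and post-test assessments".
- **Exclusion:** "Those lost to post tests will be excluded".
- **Attrition analysis:** under stated conditions, "subsequent analyses will be conducted by using the last observation carried forward (LOCF) to assess the effects of attrition". The closing sentence describes these analyses as keeping patients lost to post-test "by imputing values for the follow-up variables for the participants who will not complete the post-test assessment".

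All four rules turn on the post-test. None says what happens to a patient who has a post-test but no 1-month follow-up.

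**The concern.** The article does not leave missing data to a later document. It names an analysis set, an exclusion, an imputation method and the patients to be imputed. These rules fit a design with a baseline and one later measurement, but the efficacy model has two later measurements.

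Two things are at stake. First, the Discussion places the expected advantage of the combined treatment at the end of therapy, which is the post-test. If the stated model is run in the usual way, valid post-test outcomes leave the analysis because of a visit missed a month later. Second, two analysts could build different data sets from the same words, and the choice would be made after the data are in.

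The authors expect loss to matter. The Discussion says the short follow-up was chosen because drop-out is high in this population. The Intervention section says the follow-up also serves to detect relapse, so absence from that visit may be related to outcome.

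**Working it through.** **Rules applied to each pattern of attendance (baseline always present)**

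| Post-test | Follow-up | Main analysis as written | Attrition analysis as written |
|---|---|---|---|
| yes | yes | in the set, usable | usable |
| yes | no | in the set, but a standard repeated-measures ANOVA omits the record | unclear: LOCF could carry the post-test forward, but the imputation sentence names only post-test non-completers |
| no | yes | excluded, although the follow-up was observed | kept; no statement on how the observed follow-up is used |
| no | no | excluded | kept; baseline carried forward |

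The first and last rows are handled coherently. The two middle rows are not: in the second, the stated set differs from the set the model can use; in the third, an observed outcome is set aside.

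**Reproducing the planned sample size**

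Inputs from the Recruitment section: power 0.95, effect size 0.40 (taken as Cohen's f), α = 0.05, stated n = 58, recruitment of about 60. Assumed, because not stated: equal arms and a correlation between occasions of ρ = 0.5.

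For the between-group test over m occasions:

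λ = f² × N × m / [1 + (m − 1)ρ], with 1 and N − 2 degrees of freedom.

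- With m = 3 and N = 58: λ = 0.16 × 58 × 3 / 2 = 13.92, power 0.956.
- With m = 3 and N = 56: λ = 13.44, power 0.9495, just short of 0.95.
- With m = 2, the smallest even N that reaches 0.95 is 64.

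So 58 is recovered with three occasions and not with two. On this reading the sample size presumes about 58 patients with all three measurements.

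**Illustration of follow-up-only loss**

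The Data Analysis section expects at least 80% retention but ties it to no occasion. I take it as post-test retention: 0.80 × 60 = 48. The further loss x at follow-up only is my assumption. Complete records = 48 × (1 − x). Power uses the formula above at the whole number below, reduced to an even total for equal arms.

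| x | 48 × (1 − x) | N for power | Power | Post-test patients set aside (48 − complete records) |
|---|---|---|---|---|
| 0% | 48.0 | 48 | 0.913 | 0 |
| 5% | 45.6 | 44 | 0.888 | about 2 to 3 |
| 10% | 43.2 | 42 | 0.872 | about 5 |
| 20% | 38.4 | 38 | 0.836 | about 10 |

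A rule written by occasion would use all 48 in the post-test contrast whatever x is.

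**The case against.** The strongest reply is that the text states no exclusion of late drop-outs. A reader might infer that patients who miss only the follow-up are dropped from both the main and the attrition analysis, and the documents do not support that. The written rule puts these patients inside the main set; they are lost only through the way a standard repeated-measures ANOVA treats incomplete records, which the article does not discuss. LOCF is named without limit to an occasion and could carry the post-test value forward. The closing sentence says whom the attrition analysis adds; it need not be a complete list of who may be imputed. The phrase follow-up variables may also loosely mean all outcomes after baseline. I accept all of this, so no count of patients lost from the LOCF analysis can be given as fact.

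A reader might also infer that an observed follow-up is overwritten when the post-test is missing. Nothing says so. The main analysis excludes such a patient, which is a different matter.

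A third tempting inference is that missed follow-ups bias the comparison in favour of VR. If relapsers stay away, the maintained gain in each arm would look better than it is. The article gives no relapse or absence rates, however, and the effect on the difference between arms can go either way, depending on the gains assumed in each arm.

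Finally, it can be said that handling of a missed last visit belongs in the full protocol or analysis plan. That would hold if the article were silent. It does state the set, the exclusion and the imputation, and they do not match its own model. The looser readings do not repair this, because under any of them the sentences need rewording.

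**Conclusion.** The point holds as a mismatch between rules and model. The analysis set defined in the Data Analysis section is not the set that a standard three-occasion mixed ANOVA can use, the treatment of a patient missing only the follow-up is unsettled in the attrition analysis, and an observed follow-up is set aside in the main analysis when only the post-test is missing.

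The size is moderate and can only be illustrated. With 48 patients at post-test and an assumed 5% to 20% follow-up-only loss, complete records fall to about 46 to 38, and power of the between-group test falls from about 0.91 to between 0.89 and 0.84. This rests on ρ = 0.5, equal arms, 80% retention read as post-test retention, and the assumed loss. If 80% already means retention to the last visit, the further deduction counts some loss twice and the effect is smaller. The figures apply to the between-group test that reproduces 58, not to the Time by Group interaction. No direction of bias between the arms is claimed.

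**What to change.** Rewrite the attrition paragraph by occasion:

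- Include every patient with a baseline and a post-test in the post-test contrast, whether or not the follow-up was attended. Either a separate post-test contrast or a repeated-measures model that accepts incomplete records will do this.
- Use every observed follow-up value, including from patients who missed the post-test.
- Where values are imputed, impute each missing occasion, and say expressly that this includes a missing follow-up after a completed post-test.
- State to which occasion the expected 80% retention refers.

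The cost is a few sentences, slightly more analysis work and a different number of patients at each occasion, which the report must show. No additional patients or data are needed.

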## Discussion

A recent review has confirmed the efficacy of CBT to treat various addiction problems (7) and, especially, GD (9). Several published clinical studies have used VR to treat different psychopathological problems (anxiety, PTSD, depression, etc.), with a lot of them underlining that CBT and VR combined could improve the efficacy of social anxiety disorder and paranoia treatments (22, 24). Indeed, VR is a methodological approach that allows to recreate a realistic ecological representation of craving-eliciting situations (34–36). However, as of yet, no clinical study of CBT and VR in GD treatment has been conducted. Keeping this background into account, the necessity to develop a new study protocol—*Alter Game*– emerged. In detail, *Alter Game* aims at developing an innovative psychological treatment for GD by using VR and verifying the efficacy of an innovative psychological treatment for GD based on the integration of traditional CBT, coupled with a novel VR approach.

Based on previous studies, suggesting that CBT and VR combined are more efficient than CBT or VR only (23, 25), we aim at confirming this evidence in gambling addiction by taking specific target variables into account, such as self-efficacy, craving, and cognitive distortions. We can hypothesize that CBT and VR combined will be more effective than CBT only. In particular, at the conclusion of the psychotherapy sessions, we expect to find a higher increase of self-efficacy and a greater reduction of cravings and cognitive distortions—in terms of effect size—in the case of the integration of CBT and VR. To better evaluate these expected results, we aim at using biofeedback in order to observe and measure the psychophysiological activation associated with cue exposure, which would allow us to overcome the limits of self-report craving questionnaires or craving Likert scales. Moreover, we already implemented a training course for the treatment providers to guarantee a correct administration of the psychotherapy protocol with the patients before the study will start.

By increasing self-efficacy and reducing gambling-related craving and cognitive distortions, we aim at reducing the risk for relapse, which represents one of the most important psychotherapeutic steps for GD. Using VR cue-exposure therapy, pathological gamblers may increase their skills to prevent a relapse, or they could improve the management of their gambling craving and identify the triggers associated with it by pinpointing its cognitive, emotional, and bodily characteristics. These skills are important to prevent relapses in gambling behavior and to increase the self-efficacy of gamblers. By decreasing gambling-related distortions, which contribute to maintaining a maladaptive emotional regulation and reinforcing the irrational beliefs about gambling outcomes and controllability (48), we aim at promoting higher levels of management regarding thoughts about gambling in general. Another important aspect to be considered is that VR will provide contexts that are typical of everyday life, contributing to the generalizability of the craving management. Several studies using VR and cue reactivity to evaluate craving and other relapse risk factors in addictions (alcohol, tobacco, drugs, etc.) underlined the influence of life context in maintaining dependence or relapsing (82–84).

Despite these strengths, some limitations must be underlined. As a limitation of the study protocol, the use of self-report measures may be affected by the lack of insight/awareness, inability to identify or articulate beliefs/thoughts, and intentional dissimulation in pathological gamblers. However, the use of self-report measures is inevitable, so we chose tests that present good psychometrics properties, and we will consider the MCMI-III validity scales to control the social desirability index and the assessment protocol validity. In order to better control these biases, future studies could consider the introduction of behavioral tasks that in the Alter Game study protocol are not included except in the therapeutic intervention section. Also, the absence of a control group (non-treatment), which could serve to better analyze the efficacy of the integrated intervention, could be a further point to be addressed in the future. A public clinical service cannot omit to offer clinical treatment to a patient with GD for ethical reasons. Moreover, there may be potential threats to the internal validity of the research design due to its longitudinality, with a possible consequent loss of patients. In line with this, we chose a 1-month follow-up to keep the patients as engaged with the study as possible, since the dropout rate in pathological gamblers is high (18, 19). We are aware, however, that this time may not permit the detection of spontaneous recovery. Furthermore, studies could implement a strategy to better control susceptibility to conditioning. Another important consideration deals with the changes due to the COVID-19 pandemic. Indeed, GD is changing: a lot of patients are addicted to online gambling, so some patients that request our treatment may not respond to our inclusion criteria, in particular regarding the type of gambling activities considered in the *Alter Game* study before the beginning of the pandemic. In the future, the development and creation of new virtual environments on online gambling may be needed. The COVID-19 pandemic also brings additional complications: wearing the surgical mask can cause fogging problems to the HMD that compromise the correct use and the ideal fruition of the immersive virtual experience. In addition, the presence of restrictions for the containment of COVID-19 (lockdown, isolation, quarantines) may hamper the possibility of maintaining the 1 session per week that would be required by the study protocol. Another limitation regards the generalizability of the integrated protocol due to the possible presence of cybersickness and specific medical problems. Indeed, patients that present cybersickness during the virtual treatment or clinical problems like epilepsy, visual or hearing impairments, vestibular or cardiovascular or neurological diseases, and schizophrenia or psychotic traits will not be granted access to CBT + VR psychotherapy. Finally, future developments could improve our virtual environments through the insertion of avatars that interact with gamblers, thanks to artificial intelligence. This will be more expensive, but it may be useful to work on the impact of social interaction in the maintenance of GD and to manage situations in which gamblers are invited to eat snacks and drink alcoholic beverages. Indeed, it is known that social isolation and a sense of loneliness are related to problematic gambling (85, 86). Therefore, inserting social interaction in virtual gambling-related environments could be an important development to treat these daily experiences that may be relapse risk factors. Subjects that are socially excluded tend to self-medicate their unpleasant emotional states [e.g., anger, sadness, and anxiety; (87)] through emotion regulation processes (88) that can incorporate gambling too (89). Moreover, some studies highlighted that there is an association between gambling and alcohol use: those who drink alcohol more frequently are more inclined to gamble and to experience negative consequences due to their gambling behavior (90–93), as well as increased speed and duration of the game session (94, 95), increased risky wagering (94, 96, 97), and more rapid depletion of available funds (94–96).

To conclude, if our expected results will be confirmed, *Alter Game* could promote new possible tools for RP therapy that may be applicable within specialist-care services for GD and within therapeutic communities. These may also be suitable for poly-addicted gamblers, given the known high comorbidity between gambling and substance use disorders (98). Indeed, if the integrated virtual therapeutic protocol proposed by *Alter Game* will be effective, it could be extended to the treatment of other addiction disorders, reinforcing the traditional RP program.

## Ethics Statement

Approval for the research was obtained from the Ethics Committee for Clinical Trials (CESC) of the Provinces of Verona and Rovigo based at the Integrated University Hospital of Verona, Italy (approval code: 3004CESC with Protocol No. 69346 of 21/12/2020). The latest revision of the Declaration of Helsinki as well as the Oviedo Declaration is the basis for the ethical conduct of the study. The study protocol is designed and will be conducted to ensure adherence to the principles and procedures of Good Clinical Practice and to comply with Italian law, as described in the following documents and accepted, by signature, by the study investigators: ICH Harmonized Tripartite Guidelines for Good Clinical Practice 1996. Directive 91/507/EEC, The Rules Governing Medicinal Products in the European Community. D. L.vo n. 211 of June 24, 2003. D. L.vo n. 200, November 6 2007. Ministerial Decree of December 21, 2007. AIFA Determination, March 20, 2008. All essential clinical records will be retained to demonstrate the validity of the study and the integrity of the data collected. The promoter of this study, in accordance with the responsibilities required by the rules of good clinical practice (Legislative Decree 211/2003) and in accordance with the laws and regulations regarding data protection (including the European Regulation on the protection of personal data 2016/679), will process the personal data that will be collected exclusively for the implementation of the study and for the purpose of device surveillance.

